### Interventions

#### Exergame

The exergame group played 11 different Unity (Unity Technologies) exergames (Turku University of Applied Sciences, Finland) developed in the BEE project. Exergame development was based on a standard postoperative rehabilitation program for TKR. The exergames were played using a motion sensor (Kinect 2.0, Microsoft Corporation) connected to a laptop (Micro-Star International) and controlled with a tablet (Lenovo). Training software (GoodLife Kiosk Trainer, GoodLife Technology) and television screens offered implementation in the homes of the study participants (Figure 3). Exergaming content and progression were built for players using PhysioTools Online (PhysioTools) exercise library software, enhanced with exergames. The player controls the games using movements similar to the standard postoperative home exercise program. The research physiotherapist instructed the participants in the exergame group to play exergames progressively several times a day for 16 weeks after discharge from the hospital (Multimedia Appendix 1). In addition, the participants were recommended to follow the standard postoperative home exercise program when they could not use exergames, such as during vacations in another locality or abroad.

**Figure 3 figure3:**
[figure not shown]
Exergame solution in rehabilitation after total knee replacement in the home setting.

The initial guidance for setting up the exergame system, using applications, and testing 2 games (the Bubble Runner and Cave Game) took place at the exercise laboratory baseline visit immediately after randomization. Face-to-face individual guidance was provided for 15 to 20 minutes by the same research physiotherapist who had conducted the baseline assessment. In addition, the study participants received a written manual on exergame equipment, setup, applications, and exergaming. The participants independently set up the exergame equipment in their homes.

Exergames were categorized according to exercise target: knee extension and flexion, knee flexion or squatting, weight shifting from side to side, stretching, and functional exergames (Multimedia Appendix 1). The knee extension-flexion games (the Cave Game and Intruders) and stretching game (the Cannon) were played in a sitting position, whereas the other games (the Rowing Game, Pick Up, Squat Pong, Bubble Runner, Hat Trick, Brick Breaker, Hiking, and Toy Golf) were played in a standing position. Detailed information on each exergame’s solution explaining the game’s course and the strategies and metrics used is provided in Multimedia Appendix 1.

The first week of the exergame protocol (Multimedia Appendix 1) was initiated on the third day after surgery. The exergames of each week were prescribed to be played in the order presented in Multimedia Appendix 1. The protocol specified 4 to 5 exergames for each intervention week. The participants were instructed to play the games prescribed several times a day. Weekly, the exergame protocol became more demanding as games became more challenging, and playing time, number of repetitions, sets, and intensity in games increased. In weeks 5-12, exergames that had once been in the exergame protocol but were not planned for the current week were further available for play as additional exergames of the week. In the last 4 weeks of the exergame protocol (weeks 13-16), the exergames were the most demanding versions, with the highest exercising doses.

#### Control

The control group underwent a standard postoperative home exercise program initially instructed by a physiotherapist in the hospital where the surgery was performed (Multimedia Appendices 1-3). The research physiotherapist instructed the control group participants to follow this standard program several times a day for 16 weeks starting after discharge from the hospital. Similar to the exergame group, guidance was provided at the exercise laboratory baseline visit immediately after randomization. Face-to-face individual guidance was provided for 5 to 10 minutes by the same research physiotherapist who had conducted the baseline assessment.

#### Postoperative Usual Care

Both groups received standard care after TKR (Multimedia Appendices 2 and 3). Standard care included a clinical visit to hospital physiotherapists or orthopedists at an average of 2 months after surgery. In addition, the artificial joint status and ability to function were monitored regularly with electronic surveys and, if necessary, conventional radiography. Surveys were taken 2 to 3 months after surgery, 1 year after surgery, and will be taken every 5 years thereafter. In addition, PA guidance based on PA recommendations [20] was also provided as a part of standard care. At the 4-month postoperative research assessment visit, the research physiotherapist briefly, in approximately 5 minutes, counseled the participants of both groups about the PA guidance of standard care and provided written gym instructions for strength training (Multimedia Appendix 1).

### Outcome Measures

#### Overview

Research physiotherapists responsible for collecting descriptive data and outcomes pre- and postoperatively were trained. Preoperative descriptive data were gathered by an initial survey, by interviewing study participants, and from medical records with the permission of the study participants. The selection of outcomes (Figure 2) adapted the recommended tests of physical function in people with knee OA [21] and were collected during exercise laboratory visits in Turku or Jyväskylä, according to the participant’s residential area. Before data collection, participants were asked about their current perceived well-being (normal, tired, or unwell) to ensure safe exercise laboratory measurements. The outcomes were collected in a permanent order during both pre- and postoperative visits. The questionnaires were collected first, followed by height and weight measurements to calculate BMI. The questionnaires were collected using the pen and paper method in the following order: Oxford Knee Score (OKS), Knee injury and Osteoarthritis Outcome Score (KOOS), World Health Organization Disability Assessment Schedule (WHODAS 2.0), and satisfaction with the operated knee. In addition, on the 2- and 4-month visits, after previous questionnaires, the Positive System Usability Scale (P-SUS) and Game User Experience Satisfaction Scale (GUESS) questionnaires were collected from participants in the intervention group. Subsequently, the assessments were performed for all participants in the following order: knee pain (visual analog scale [VAS]), knee range of motion, Short Physical Performance Battery (SPPB), TUG test, 10-meter walking speed, and isometric knee extension and flexion strength. Sitting balance was measured using a prototype measuring device (SmartChair, Tohoku University) in the TUG and SPPB sit-to-stand tests. Finally, interviews were conducted. Data regarding exercise time and dose throughout the intervention period and PA through study completion were gathered by self-reported structured diaries and exergame time and dose data by game computers. The outcome assessments and interviews are described in detail in the *Primary Outcomes*, *Secondary Outcomes*, and *Qualitative Data* sections.

To minimize the amount of missing data owing to the COVID-19 pandemic, the principal investigators approved changes to the data collection method. Consequently, all data to be collected using the pen and paper method were collected by mail from the participants during the lockdowns and from the participants who, on their own, did not visit the exercise laboratory after the lockdown. The change to the data collection method did not require a modification of the ethical statement or hospital permission.

#### Primary Outcomes

Changes in knee function and pain were assessed using the OKS questionnaire [22]. OKS is a short, reproducible, valid, and sensitive questionnaire used to assess clinically important changes after TKR surgery [23]. Each of the 12 items was scored from 0 to 4, with 4 being the best outcome. When summed, the overall scores ranged from 0 to 48 points, with higher scores indicating better function and lower knee pain.

The TUG test was used to assess changes in mobility [24]. The TUG test was performed twice at maximum speed, with the shoes on. Time in seconds was measured using a stopwatch. Both results were recorded, and a better result (shorter time in seconds) was used. A lower TUG test time indicated better mobility.

#### Secondary Outcomes

Walking was assessed with a 10-meter walking test [25] performed 4 times with shoes on: twice with normal speed and twice with fast speed with a 2-meter flying start. Possible use of walking aids was also recorded. The time in seconds was measured using photocells. All results in seconds were recorded and reported as the walking speed (m/s). Better results at normal and fast speeds (higher value of m/s) were used. Higher speed in the 10-meter walking test indicated better walking performance.

Lower extremity performance was assessed using the SPPB test [26], which includes 3 subtests: static balance in 3 different positions, 4-meter walking time, and 5 repetitions of sit-to-stand. The balance test was performed without shoes. The walking test was performed at normal speed, and the sit-to-stand test was performed at fast speed, and both these tests were performed with shoes on. The possible use of a walking aid during the test was also recorded. All subtest results were recorded in seconds and scored from 0 to 4 points, leading to a maximum of 12 points. Higher SPPB test scores indicate better lower extremity performance.

Muscle strength was assessed with isometric knee extension and flexion forces collected using a Metitur Good Strength dynamometer in Jyväskylä (Newton [N]) and a Con-Trex Multijoint dynamometer (Newton-meter [Nm]) in Turku. Knee extension and flexion forces were measured from each lower limb in the sitting position, with the knee angle at 60° of flexion. The measurement sequence was as follows: (1) knee extension, (2) knee flexion force from the nonoperated lower limb, (3) knee extension, and (4) knee flexion force from the operated lower limb. The participants performed 4 warm-up and training contractions with moderate force, after which 4 contractions with maximal force were measured. Thereafter, the performances were repeated until the force improved to <50 N during the knee extension contraction and <20 N during the knee flexion contraction. One contraction lasted approximately 3 seconds, and there was a 30-second break between contractions. All maximal force results were recorded. In addition, after completion of the sets of contractions of the lower limb (eg, knee extensions and flexions of the operated lower limb), the participants were asked if the pain impaired their performance. The direction of painful performance (ie, extension, flexion, or both) and pain intensity on a scale of 1 to 10 were recorded. The best results for knee extension and flexion forces (Nm or N) were used. For analysis, N values were calculated as Nm with the formula Force (N) × lever arm length of the leg (m) and normalized based on body weight (Nm/weight). A higher value in the isometric knee extension and flexion tests indicated better muscle strength.

The range of knee joint flexion and extension was measured using a universal goniometer [27,28]. Measurements were performed on the operated knee in the supine position. First, active and passive knee flexion were measured, followed by active and passive knee extensions. The results were recorded in degrees; a smaller result in extension and larger result in flexion indicated a better joint range of motion.

Knee pain was assessed using the pen and paper version of the VAS [29] by asking participants to rate the average knee pain over a week. The VAS ranges from 0 to 100, indicating no knee pain and the worst possible knee pain, respectively.

Disability was evaluated using the self-reported WHODAS 2.0 questionnaire [30] including 12 items. The scale ranges from 0 to 4 per item, indicating values from “no difficulty” to “extreme difficulty,” and the total score ranges from 0 to 48 points. A lower total score on the WHODAS 2.0 indicated better function.

The KOOS questionnaire [31] includes 5 subscales: pain, other symptoms, quality of life, ADL, and sport and recreation function. The 5-point Likert scale ranged from 0 to 4 for each subscale. The maximum score on each subscale was 100 points. A higher score on the KOOS questionnaire indicated less knee pain and associated problems.

Exergame experience was evaluated using the GUESS [32] and the 10-item P-SUS [33] questionnaires. GUESS includes 9 subscales that assess usability or playability, narratives, play engrossment, enjoyment, creative freedom, audio esthetics, personal gratification, social connectivity, and visual esthetics. The questions were scored from 1 to 7, indicating values from “strongly disagree” to “strongly agree.” In addition, a score of 8 indicates “not applicable.” P-SUS questions were scored from 1 to 5, indicating values from “strongly disagree to “strongly agree.” A higher score on the GUESS and P-SUS questionnaires indicated a more positive experience of the exergames played.

Outcomes related to exercise adherence were collected using a self-reported structured diary and a game computer. Participants filled in the exercise diary daily for the exergame and standard home exercise adherence (number and duration of exercise sessions in minutes). This will be summed as days, sets, and minutes of exergaming and standard exercising per week. Minutes per week will be calculated as metabolic equivalent hours per week [34-36]. In addition, exergame adherence was measured based on the game computer data gathered during each exergame session (name of exergame, duration, timestamp, and game score). Adherence from game computer will be calculated as days, sets, and minutes of performed exergaming per week. Longer exercise duration, that is, minutes per week, indicated a higher level of commitment to exercise. In addition, adherence throughout the intervention period will be reported as the percentage of completed exercise days compared with the total number of days.

PA was measured using a structured PA diary, which the participants completed daily from baseline to 12 months. The diary form sought data on each activity’s mode, intensity, and duration. Leisure time PA and PA related to daily errands or commuting are reported separately. PA will be calculated as the metabolic equivalent hours per week and month by multiplying each marked activity by self-evaluated intensity (1, light; 2, moderate; and 3, vigorous), according to Ainsworth et al [34].

Satisfaction with the operated knee was assessed using the following question: “How satisfied are you with your operated knee?” Response options were “very satisfied,” “satisfied,” “dissatisfied,” and “very dissatisfied.”

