### Sample Size

The intended sample size (n=100) of the BEE-RCT was based on the primary outcome, the OKS [22]. Assuming a mean difference of 5 (SD 8) points [40] in a change in the OKS between the groups at 6 to 12 months [40,41], a sample size of 42 in the intervention and control groups was required to detect differences between groups at an α of .05 and reach power of 80%. The dropout rate was estimated to be 10%; consequently, a minimum of 100 participants were needed to be recruited. In 2020, the COVID-19 pandemic decreased the number of elective surgeries, such as TKR, and there were lockdowns in exercise laboratories. Due to this, recruitment slowed in the spring of 2020 and was completely stopped for 3 months because of lockdowns. Consequently, the trial failed to recruit the intended sample size of participants.

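### As worded, the physical activity rule multiplies by a 1-2-3 intensity code, which gives an intensity-weighted score and not MET hours

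*Protocol article*

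**What the plan says.** The PA paragraph under Secondary Outcomes describes a daily diary kept from baseline to 12 months: "The diary form sought data on each activity’s mode, intensity, and duration". Leisure-time activity is reported separately from activity related to errands or commuting. The paragraph then gives the derivation. The unit is MET hours per week and month, and these are to be obtained "by multiplying each marked activity by self-evaluated intensity (1, light; 2, moderate; and 3, vigorous"), followed by a reference to source [34]. The article reproduces no MET values from that source.

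The preceding paragraph, on exercise adherence, uses the same unit for a different outcome: "Minutes per week will be calculated as metabolic equivalent hours per week". It cites sources [34-36] and mentions no 1-2-3 code.

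Protocol Version and Amendments records that PA diaries replaced activity monitors before data collection. The diary derivation is therefore the only PA measure that the article describes.

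**The concern.** A MET is a multiple of the resting metabolic rate. MET hours are the MET value of an activity times the hours spent on it. The codes 1, 2 and 3 only rank the participant's own rating as light, moderate or vigorous. Hours times code equals MET hours only if those three categories happened to lie at exactly 1, 2 and 3 METs for every activity. The diary records mode, which is what would allow an activity-specific value, yet the rule gives mode no role. Duration is not named in the product either, although the unit implies it.

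What is at stake is the meaning of the reported figure. Background and Rationale argues that PA stays below recommended levels after knee replacement. A reader will naturally set a figure labelled MET hours against MET-based recommendations or other studies. If the figure is really a 1-2-3 weighted sum, that comparison is not valid.

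**Working it through.** The article gives no PA figure to reproduce, so the check is to apply the rule as worded and compare it with MET hours.

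**Inputs from the article:** multipliers 1 (light), 2 (moderate) and 3 (vigorous); diary fields mode, intensity and duration; unit MET hours.

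**Inputs that are assumptions:** light 1.5-2.9 METs, moderate 3-5.9 METs, vigorous at least 6 METs. The article states none of these.

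**Formulas**
- Literal rule: score = sum of hours × code (hours supplied by the unit).
- MET hours = sum of hours × MET value.
- Understatement for one category = 1 − code / MET value.

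| Category | Code | Assumed METs | Understatement on the literal reading |
|---|---|---|---|
| Light | 1 | 1.5 to 2.9 | 1 − 1/1.5 = 33% to 1 − 1/2.9 = 66% |
| Moderate | 2 | 3 to 5.9 | 1 − 2/3 = 33% to 1 − 2/5.9 = 66% |
| Vigorous | 3 | at least 6 | at least 1 − 3/6 = 50% |

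**Two illustrative weeks**
- 3.5 h moderate. Literal: 3.5 × 2 = 7. MET hours: 3.5 × 3 = 10.5 to 3.5 × 5.9 = 20.7.
- 5 h light and 2 h moderate. Literal: 5 × 1 + 2 × 2 = 9. MET hours: 5 × 1.5 + 2 × 3 = 13.5 to 5 × 2.9 + 2 × 5.9 = 26.3. The literal score is 9/13.5 = 67% to 9/26.3 = 34% of MET hours.

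**The other reading.** If mode and code together select a MET value from source [34], and that value is multiplied by hours, the result is MET hours and the error is 0%.

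The wording does not settle the choice. For the literal reading: the sentence names the operation as multiplication, names self-rated intensity as the multiplier, and lists its values. For the look-up reading: the sentence refers to a source for the method, and the diary collects mode, which the literal rule would not need.

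**The case against.** The strongest reply is that the sentence is loosely worded and not wrong. It defers to a cited source, the diary holds all that is needed for a proper conversion, and the codes may be no more than diary labels. The source is not at hand, so the literal reading cannot be confirmed as the plan. This stands, and it makes the size conditional. It does not remove the point, because the sentence itself says that the code multiplies.

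A second reply is that a condensed article may leave MET tables to a fuller document. That is fair for the values themselves. But the article goes further and states a rule, and that rule as written does not produce the unit it names.

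Three stronger inferences are tempting, and the documents do not support them:
- **Light activity is scored the same as rest.** A multiplier of 1 does equal the resting rate by definition. But the diary sums marked activities, so unrecorded rest adds 0 while an hour of light activity adds 1 on the literal reading. The two are not scored alike.
- **The comparison between arms is distorted because one arm plays exergames.** Exergaming and standard home exercise are captured in the exercise diary and, for exergames, the game computer. Nothing shows that the 1-2-3 rule is applied to them. Moreover, with illustrative values of 2, 4 and 7 METs the understatement is 1 − 1/2 = 50%, 1 − 2/4 = 50% and 1 − 3/7 = 57%. That is close to a common scale factor and would largely preserve relative differences between arms.
- **The adherence outcome has the same fault.** Its paragraph converts minutes with sources [34-36] and contains no 1-2-3 multiplier.

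**Conclusion.** The point holds in a limited form. Followed as worded, the PA rule yields an intensity-weighted activity score that is mislabelled as MET hours. The look-up reading remains possible and would leave nothing to correct but the sentence.

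On the literal reading only, and under the assumed MET ranges, light and moderate activity are understated by about 33-66%. On the look-up reading the error is zero. No single corrected figure can be derived, because the article gives no MET values.

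The harm is to the level of the figure and its comparability with outside standards, for one secondary outcome. The primary outcomes are the Oxford Knee Score (OKS) and the Timed Up and Go test, and the sample size "was based on the primary outcome, the OKS", so neither is touched.

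**What to change.** Reword the derivation so that each PA diary entry receives the MET value for its recorded mode and intensity from source [34], is multiplied by its duration in hours, and is summed per week and per month. State that the codes 1-3 serve only to select the value.

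If the investigators prefer to keep 1-3 as the multiplier, call the result an intensity-weighted activity score, and do not compare it with MET-based recommendations.

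The first option uses only fields that the diary already collected. Its cost is some analyst time to recode the diaries. If the codes were meant as look-up categories all along, a clarifying sentence is enough.

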#### Qualitative Data

Individual interview data on patients’ perspectives on rehabilitation and exergames were collected 4 and 12 months after the operation. Face-to-face interviews were recorded, and laddering notations were used. Owing to the COVID-19 pandemic, phone interviews were conducted as necessary. All participants were invited to participate in the interviews. The laddering interview technique supports the understanding of the user’s perspective [37]. The technique is based on the personal construct theory [38], which emulates human beings’ mental models. The laddering interviewing technique operationalizes the personal construct theory by providing a means to investigate system attributes, consequences (reasoning) for system use, and values or goals that drive its use [37]. The laddering interview process by Tuunanen and Peffers [39] was followed. First, participants were given a list of stimuli (Multimedia Appendix 4) intended to suggest ideas about possible recovery experiences of participants to enable brainstorming [37]. Second, the interviewees were asked to select 2 stimuli that they perceived as the most important to them. The interviewer proceeded to ask the participant to explain why each experience was important by asking questions such as “why” and “why that would be important.” The ladder data were recorded as attribute-consequence-value chains, as presented by Tuunanen and Peffers [39]. The interview recordings are also transcribed to later enable other qualitative approaches in the analysis.

